### 2.9. Missed Sessions and Early Termination of Participation

Participants who, for any reason, miss a scheduled brain stimulation session or assessment will be given the opportunity to make it up the following day (including weekends if necessary). If they withdraw or are removed from the study at any phase, they will discontinue all research-related activities, including termination of the tRNS and all assessments that are directly related to the study. Clinical care will be unaffected.

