### 2.6. Sample Size Considerations

The sample size was calculated by a priori analysis in G * Power, version 3.1.9.7 (The G*Power Team, Düsseldorf, Germany).

Because the design of this project has never been employed in children and adolescents with MLD, we could refer only to a pilot study that determined the effects of tRNS, combined with cognitive training, in children with MLD [66]. However, the study included 12 children with a medium effect size but differs in several aspects from ours: the number of tRNS sessions, number of groups, and cognitive training. To be conservative and start from these premises, we calculated the expected effect size (f) to low and estimated it at 0.15.

With an estimated f = 0.15, α value = 0.05 (i.e., probability of false positives of 5%), and β = 0.80 (i.e., at least 80% power), the sample size that was required for repeated-measures analysis of variance (RM ANOVA) with 3 groups (Frontal Group vs. Parietal Group vs. Sham Group) and 4 measurements (T0 vs. T1 vs. T2 vs. T3) was 78 (i.e., 26 per group). Considering a 30% dropout rate in the follow-ups, we will plan to recruit a total of 102 participants (i.e., 34 per group).

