### 2.8. Protection of Risks

To minimize any risk that is associated with tRNS, participants will be monitored throughout the stimulation sessions and asked to report any discomfort. If the scalp sensation is uncomfortable, the stimulation will be stopped. In the event of a headache, the stimulation will be stopped. All tRNS sessions will be administered and supervised continuously by a trained experimenter. There are no reports of seizures having been induced by tRNS in human participants. However, to avoid any chance of seizure, a prior history of neurological disorders is an exclusionary criterion for our study, and no participants will have a history of seizure. The risks that are associated with cognitive training and assessment are minimal. Nevertheless, breaks will be offered if participants experience frustration with the tasks.

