### 3.2. Statistical Analysis

The Shapiro–Wilk test will be used to test the normality of the data, and Levene’s test will be performed to analyze the homogeneity of the variances. When the data are normally distributed and the assumption of homogeneity is not violated, parametric analyses will be computed. When one assumption is not met, nonparametric tests will be conducted or log-transformation of the distribution will be applied, if appropriate. When appropriate, sphericity will be verified by Mauchly’s sphericity test. When sphericity is not met, Greenhouse–Geisser correction will be applied.

Chi-square analysis will be used to compare groups with regard to demographics, blindness, and safety measures (categorical variables).

Linear mixed-effects models, which account for within-subject correlations more optimally than analysis of variance and automatically handle missing values, allowing maximum use of available data [93], will be run to compare groups for primary (continuous variables: number line subtest) and secondary outcomes (continuous variables: arithmetic, neuropsychological, and psychological measures). The R package lme4 v1.1–17 [94,95], which estimates model parameters using restricted maximum likelihood estimation and computed *p*-values per Satterthwaite’s method [96], will be used. The linear mixed-effects models will include Group (Frontal, Parietal, and Sham) and Time (T0, T1, T2, T3) as fixed factors and Participants as the random factor. Baseline performance will be included as a covariate in our model, because it allows us to make better adjustments for minor differences in pretreatment means. The same analysis will be performed for the training accuracy data, including Group (Frontal, Parietal, and Sham) and Day (from 1 to 10) as fixed factors and participants as the random factor.

Pearson’s correlation will be used to determine whether and the extent to which arithmetic improvements are related to changes in neuropsychological measures, psychological measures, and spectral power of EEG frequency bands at T1, T2, and T3 (from T0).

The statistical results will be corrected for multiple comparisons by Bonferroni’s correction where appropriate.

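### Section 2.9 ends all outcome and safety assessment for any child who withdraws or is removed, so obtainable T1–T3 data are lost and the analysis leans further on missing at random

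*Protocol article*

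**What the plan says.** Section 2.9 has two parts. A child who misses a stimulation session or an assessment "will be given the opportunity to make it up the following day" and so stays in the trial. The second part opens "If they withdraw or are removed from the study at any phase" and continues "they will discontinue all research-related activities, including termination of the tRNS and all assessments that are directly related to the study". It covers removal by staff as well as withdrawal by the family.

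Four other places bear on this:
- Section 2.3 puts the end of treatment and T1 on the same day (Day 12), T2 on Day 19 and T3 on Day 102.
- Section 2.6 inflates the sample for loss: "Considering a 30% dropout rate in the follow-ups, we will plan to recruit a total of 102 participants (i.e., 34 per group").
- Section 3.2 analyses the primary and secondary outcomes with linear mixed models, chosen partly because they "automatically handle missing values, allowing maximum use of available data".
- Section 2.5.6 collects a side-effect questionnaire after every session and at T1, T2 and T3. Section 2.7 adds that adverse effects are recorded for the whole study and that participants are followed for them after it ends.

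**The concern.** Leaving the intervention and leaving measurement are different events, and section 2.9 treats them as one. A family that refuses further contact must be let go. A child removed by staff, or whose family wants no more stimulation but would attend a visit, could still give a Number Line score and a safety questionnaire. Under the rule as written, those data are not collected.

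This is a data-collection rule, so no analysis plan can repair it: sensitivity analyses can explore assumptions about absent outcomes but cannot recover them. The mixed model is valid if loss depends only on what was observed. A child who leaves during Days 1 to 12 offers it only T0. At stake are the comparison of active with sham at T1 to T3 and the first research objective in section 1.3, the long-term safety and feasibility of repeated sessions.

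**Working it through.** **1. The plan's own figures.** Inputs from section 2.6: f = 0.15, alpha 0.05, 80% power, 3 groups, 4 measurements. Assumed, because not given: correlation 0.5 between measurements and sphericity. For the group-by-time interaction the noncentrality is f² × N × m / (1 − rho) = 0.0225 × 78 × 4 / 0.5 = 14.04, with 6 and (78 − 3) × 3 = 225 degrees of freedom. Power is 0.801, so 78 is reproduced. The recruitment target is 78 × 1.3 = 101.4, rounded up to 102.

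**2. How many children could the rule touch?** The planned loss is 0.30 × 102 = 30.6, about 31 children. That is a ceiling on planned loss, not an estimate of what the rule causes. Treatment ends on the day of T1, so a child lost between T1 and T3 has no intervention left to stop. Such a child is usually lost because the family does not return, and changing 2.9 would not bring that family back. The rule bites on children who stop or are removed during Days 1 to 12, and on later removals by staff. The article gives no number for either.

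**3. Bias in a plain comparison of observed means.** Let p be the share lost in an arm and D the gap, in SD, by which the children lost do worse than those observed. The bias in active minus sham is p(active) × D(active) − p(sham) × D(sham). All loss rates and deficits here are assumptions, with the same D in both arms.

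| Loss, active / sham | D = 0.25 | D = 0.5 | D = 0.8 |
|---|---|---|---|
| 30% / 30% | 0 | 0 | 0 |
| 35% / 20% | 0.15 × 0.25 = 0.04 | 0.15 × 0.5 = 0.075 | 0.15 × 0.8 = 0.12 |
| 40% / 10% | 0.30 × 0.25 = 0.075 | 0.30 × 0.5 = 0.15 | 0.30 × 0.8 = 0.24 |

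Swapping the two loss rates reverses the sign.

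**4. Bias when earlier visits are kept.** The plan does not compare observed means, so a second check is needed. I simulated 400,000 children with no treatment effect, four visits and correlation 0.5. In one arm 30% of T3 values were missing, with log-odds of loss falling by 1 per SD of the driving score; the other arm was complete. A regression of T3 on the retained earlier visits stands in for the mixed model.

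| Loss at T3 depends on | Completers only | T0 and T1 kept | Only T0 kept |
|---|---|---|---|
| T1 score | 0.13 SD | 0.00 SD | 0.07 SD |
| T3 score itself (unseen) | 0.25 SD | 0.18 SD | 0.20 SD |

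The model removes the bias when the score that drives loss has been recorded. It does not when that score is unseen, or when the child left before T1. Assessing children after they leave the intervention shrinks both of these groups.

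**The case against.** Several stronger readings are tempting, and the article does not support them.

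- **That the trial becomes a completers' comparison.** Section 3.2 uses every recorded visit, and nothing excludes non-completers. If loss follows an observed T1 score, the check above gives about 0.00 SD, against 0.13 SD for completers.
- **That a child whose stimulation is stopped leaves the study.** Section 2.8 says "In the event of a headache, the stimulation will be stopped" but does not say that the child is then removed. Section 2.9 is triggered by leaving the study, and its first part keeps a child who misses a session.
- **That all of the 30% is due to this rule.** Section 2.6 words it as "Considering a 30% dropout rate in the follow-ups", and most of the follow-up period comes after treatment has ended.
- **That loss is related to arm and inflates efficacy.** Sham children have the same electrodes and a 30-second ramp (section 2.4.2), and section 3.3 expects no group difference in safety or blinding. Arm-related loss is possible but not shown, and its direction is unknown.
- **That late adverse effects are under-counted.** Section 2.7 promises follow-up for adverse effects. How that fits with the end of all assessments in 2.9 is unclear, so the two need reconciling; a shortfall is not established.

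It can also be said that the full protocol may define removal, and an analysis plan may specify analysis as randomised and missing-data sensitivity analyses. Their absence from an article is no fault. But the rule printed in 2.9 is explicit, and it governs which data will exist.

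**Conclusion.** The point holds in a limited form. Section 2.9 discards outcome and safety data that could be collected from children who leave the intervention without refusing assessment. For them the analysis must rely on missing at random, and those gone before T1 have no post-baseline outcome.

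The number affected is unknown. The bias is also unknown in size and sign: zero with equal loss and equal deficit in each arm, and 0.18 to 0.20 SD in the illustration where 30% of one arm is lost according to the unseen T3 score. That figure rests on an assumed correlation of 0.5, an assumed strength of selection and loss confined to one arm, and it applies the full 30% to one arm, so it is not a forecast. I do not express it as a share of the planned effect, because the f in section 2.6 converts to a group difference only under an assumed pattern over time.

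This is a cheap improvement to a stated rule. It does not show that the planned comparison is invalid.

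**What to change.** In section 2.9, separate two events: stopping or being removed from the intervention, and withdrawing consent or assent for assessment. Children in the first category remain in their randomised group, are invited to T1, T2 and T3 with at least the Number Line subtest and the safety questionnaire, and are analysed as randomised. Assessment ends only when consent or assent for it is withdrawn. State in the same place how this fits with the adverse-effect follow-up in section 2.7.

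The rules for stopping stimulation in section 2.8 are left as they are.

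The cost is a sentence or two in the protocol and the consent form, visits that are already planned, and a few extra contacts with families who have stopped treatment. Families that decline assessment will still be lost, so reliance on missing at random is reduced and not removed.

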### 2.10. Study Monitoring and Data Management

The principal investigator (or the ethics committee) will identify a study monitor who is assigned to follow this study per this Clinical Trial Protocol [European guidelines for Good Clinical Practice (CPMP/ICH/135/1995) and Decree-Law Italian Minister of Health, 15 July 1997]. The Investigator agrees to provide reliable data and all information that is requested by the Protocol in an accurate and legible manner according to the instructions that are provided and ensure direct access to source documents to ethics committee representatives. If any particular circuit must be defined, attention should be paid to the confidentiality of the participants’ data that are to be transferred.

The principal investigator may appoint other individuals as deemed appropriate as subinvestigators to assist in the conduct of the Clinical Trial per the Clinical Trial Protocol. All sub-investigators shall be timely appointed and listed. The subinvestigators will be supervised by and under the responsibility of the principal investigator. The principal investigator will provide them with a Clinical Trial Protocol and all necessary information.

The participants’ personal data will be anonymous and coded. The hard files will be placed in a closed drawer. The database will be protected by password. The investigators will allow the monitoring of the data at an appropriate frequency. The original documents will be available at any time to be verified by the clinical monitor and regulatory authority.

## 3. Data Analysis

### 3.1. EEG Preprocessing

EEG preprocessing will be performed separately for data that are collected before (T0) and after the interventions (T1, T2, T3), with the examiner being blinded to the stimulation conditions for all preprocessing steps. First, the EEG file will be imported into MATLAB (R2020b, The Mathworks) using the EEGlab toolbox (eeglab2021.0) [92], and channels will be located on the scalp model using the NE_EEGLAB_NIC_Plugin_v1.9 plugin (Neuroelectrics). Data will be band-pass-filtered from 1 Hz (high-pass) to 70 Hz (low-pass). The line noise (~50 Hz) will be removed. Next, the data will be divided into windows of 1 sec (epochs), and EEG epochs with muscle, electrode, and blinking artifacts will be manually removed. Independent component analysis will be conducted, and any period of nonindependence between components will be identified by eye. The spectral power for each epoch in four frequency bands [theta (θ) = 4–7.99 Hz; alfa (α) = 8–12.99 Hz; beta (β) = 13–29.99 Hz; gamma (γ) = 30–50 Hz] will be computed and averaged across epochs for each participant.

### 3.2. Statistical Analysis

The Shapiro–Wilk test will be used to test the normality of the data, and Levene’s test will be performed to analyze the homogeneity of the variances. When the data are normally distributed and the assumption of homogeneity is not violated, parametric analyses will be computed. When one assumption is not met, nonparametric tests will be conducted or log-transformation of the distribution will be applied, if appropriate. When appropriate, sphericity will be verified by Mauchly’s sphericity test. When sphericity is not met, Greenhouse–Geisser correction will be applied.

Chi-square analysis will be used to compare groups with regard to demographics, blindness, and safety measures (categorical variables).

Linear mixed-effects models, which account for within-subject correlations more optimally than analysis of variance and automatically handle missing values, allowing maximum use of available data [93], will be run to compare groups for primary (continuous variables: number line subtest) and secondary outcomes (continuous variables: arithmetic, neuropsychological, and psychological measures). The R package lme4 v1.1–17 [94,95], which estimates model parameters using restricted maximum likelihood estimation and computed *p*-values per Satterthwaite’s method [96], will be used. The linear mixed-effects models will include Group (Frontal, Parietal, and Sham) and Time (T0, T1, T2, T3) as fixed factors and Participants as the random factor. Baseline performance will be included as a covariate in our model, because it allows us to make better adjustments for minor differences in pretreatment means. The same analysis will be performed for the training accuracy data, including Group (Frontal, Parietal, and Sham) and Day (from 1 to 10) as fixed factors and participants as the random factor.

Pearson’s correlation will be used to determine whether and the extent to which arithmetic improvements are related to changes in neuropsychological measures, psychological measures, and spectral power of EEG frequency bands at T1, T2, and T3 (from T0).

The statistical results will be corrected for multiple comparisons by Bonferroni’s correction where appropriate.

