For all questionnaires, raw scores are converted into z-scores. Higher scores indicate better outcomes and will be considered as an improvement.

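### Section 3.2 leaves a normality-test switch unreconciled with an unconditional mixed model, so the primary analysis can change after the data are seen

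*Protocol article*

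**What the plan says.** All the relevant text is in the protocol article, section 3.2 (Statistical Analysis), apart from the design figures in section 2.6.

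- The opening paragraph sets the preliminary tests: "The Shapiro–Wilk test will be used to test the normality of the data, and Levene’s test will be performed".
- It then states the condition: "When the data are normally distributed and the assumption of homogeneity is not violated, parametric analyses will be computed".
- It then states what happens otherwise: "When one assumption is not met, nonparametric tests will be conducted or log-transformation of the distribution will be applied, if appropriate".
- A later paragraph says that linear mixed-effects models "will be run to compare groups for primary (continuous variables: number line subtest) and secondary outcomes". No condition is attached.
- One reason given for choosing these models is that they "automatically handle missing values, allowing maximum use of available data".
- Baseline is adjusted for: "Baseline performance will be included as a covariate in our model".

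The section gives no significance level for the preliminary tests. It does not say whether they apply to each group-by-visit cell, each visit, a pooled sample or the model residuals. It does not name the nonparametric test or say how to choose between that test and the log transformation.

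**The concern.** A linear mixed model is a parametric analysis, and nothing in the opening paragraph exempts the primary outcome. A reader who applies that paragraph literally would drop the mixed model for the Number Line subtest if either assumption failed. A reader who starts from the later paragraph would fit it regardless. The plan supports both courses, and the choice would be made with the data in hand.

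The trigger also tests the wrong quantity. The model assumes roughly normal residuals and random effects. Non-normal raw scores do not by themselves violate that, and a pass on raw scores does not establish it.

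Two things are at stake. The primary result could come from a different and less powerful test chosen after inspection of the data. Secondary outcomes could also end up analysed by different methods because of chance results in preliminary tests, which would make them hard to compare.

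**Working it through.** **1. The plan's own figure.** Section 2.6 states that the sample size for "3 groups (Frontal Group vs. Parietal Group vs. Sham Group) and 4 measurements (T0 vs. T1 vs. T2 vs. T3) was 78", with f = 0.15, α = 0.05 and 80% power. For the group-by-time interaction in a repeated-measures ANOVA:

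- λ = f²·N·m/(1 − ρ) = 0.0225 × 78 × 4 / 0.5 = 14.04
- df1 = (3 − 1)(4 − 1) = 6; df2 = (78 − 3)(4 − 1) = 225
- power = 0.801

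The figure of 78 (26 per group) reproduces. The correlation ρ = 0.5 and sphericity are assumptions, because the article gives neither.

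**2. How often ideal data would trigger the switch.** Assume a 0.05 level for every preliminary test. If k tests were independent, the chance of at least one failure in perfectly normal, equal-variance data is 1 − 0.95^k. Visits on the same child are correlated, so this was also simulated: 4,000 trials per setting, 26 and 34 per group, within-child correlation 0, 0.5, 0.7 and 0.9.

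| Reading of the rule | k | If independent | Simulated |
|---|---|---|---|
| Shapiro–Wilk in each of 3 × 4 = 12 cells | 12 | 46% | 36–46% |
| The same, plus Levene at each of 4 visits | 16 | 56% | 44–57% |
| Shapiro–Wilk per visit on group-centred data, plus Levene per visit | 8 | 34% | 25–36% |
| One Shapiro–Wilk on model residuals, plus one Levene | 2 | 10% | 9–10% |

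The last row is generous to the plan, since the text speaks of the data and not of residuals. Under the article's wording, the false-trigger rate can therefore lie anywhere from about 9% to 57%.

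**3. What the nonparametric branch could cost.** The test is unnamed, so take an ordinary two-sample rank test of one active arm against Sham at T1, with 26 per arm and normal data. Set the effect so that the baseline-adjusted analysis has 78% power. Its standardised effect is then about 1.96 + 0.77 = 2.73. Relative to that analysis:

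- T1 alone multiplies the effect by √(1 − ρ²).
- Change from baseline multiplies it by √((1 + ρ)/2).
- The rank test multiplies it further by √(3/π) = 0.977.

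Results, with power = Φ(value − 1.96):

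- ρ = 0.5, T1: 2.73 × 0.866 × 0.977 = 2.31, power about 64%. Change has the same factor, so also about 64%.
- ρ = 0.7, T1: 2.73 × 0.714 × 0.977 = 1.90, power about 48%.
- ρ = 0.7, change: 2.73 × 0.922 × 0.977 = 2.46, power about 69%.

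Repeated simulations, with adjusted power set at 77–79%, gave 47–66% for the rank test on T1 and 63–70% for the rank test on change. The approximation agrees. The loss comes mainly from dropping the baseline covariate or replacing it with a simple difference. It occurs even when the data are exactly normal, that is, when the switch was triggered by chance.

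**4. The log branch.** A logged outcome can be put in the same mixed model with the same covariate and the same handling of incomplete records. None of the loss in step 3 applies to it.

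**The case against.** The strongest defence is that the mixed-model paragraph is unconditional and specific. The opening paragraph is general and might be meant for other tests, such as the Pearson correlations. That stands in part: a reader might infer that the mixed model is used only if the tests are passed, and the article does not say so. What it leaves is two statements that have not been reconciled.

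Other stronger readings also go beyond the text:

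- **That normal data would fail about half the time.** This needs testing in every cell at 0.05, and neither is stated. Failure of one assumption is not the same as one small p-value among twelve.
- **That the fallback discards baseline adjustment and missing-data handling.** This is true of an ordinary rank test, but not of the log branch. A rank-transformed outcome in the same model would keep both as well.
- **That the analysis would shrink to the roughly 71 of 102 children left after 30% dropout.** This applies only to tests that need every visit. A rank test at T1 uses every child with T1 data; T1 is the last intervention day, and section 2.6 places the dropout in the follow-ups.
- **That logs cannot be taken of negative z-scores, and that Mauchly and Greenhouse–Geisser do not belong with a mixed model.** Both are guarded by the article's own qualifiers. The z-score scales are secondary outcomes.

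It can also be said that naming the test, its level and the diagnostics is normally left to a statistical analysis plan. That is fair for those details. It does not answer the main point, because the article does state a decision rule, and that rule conflicts with its later paragraph.

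**Conclusion.** The point holds in limited form and should be fixed. Section 3.2 contains a data-dependent rule that, read as written, reaches the primary mixed model and conflicts with the unconditional statement further down. It tests raw scores for an assumption that concerns residuals and random effects.

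The false-trigger rate is about 9–10%, 25–36% or 44–57%, depending on a unit of testing that the article does not give and on an assumed 0.05 level. These rates are for ideal data. The article gives no distribution for the Number Line score, so the rate for the real outcome cannot be calculated.

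If an ordinary rank test were substituted, power of about 78% would fall to about 47–66% (T1) or 63–70% (change), with 26 per arm and an assumed correlation of 0.5–0.7. That cost is conditional on the branch taken. The conflict between the two statements, and the freedom to choose after seeing the data, do not depend on any of these assumptions.

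**What to change.** Amend section 3.2, before unblinding, as follows:

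- State that the baseline-adjusted linear mixed model is the primary analysis of the Number Line subtest, and the analysis of the continuous secondary outcomes, whatever any preliminary test shows.
- Replace the Shapiro–Wilk and Levene switch with a check of the fitted model's residuals, reported but not used to change the primary method.
- Name one sensitivity analysis for the primary outcome that keeps the model structure: for example a cluster bootstrap, robust standard errors, or a rank-transformed outcome in the same model. Any transformed, robust or rank-based analysis belongs there.

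The cost is a few sentences of analysis text and one additional run. Design, sample size and data collection are unchanged.
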